### 8.3. Collection and reporting of adverse events

All adverse events have to be reported in the toxicity case report form, graded according to the Common Terminology Criteria for Adverse Events (CTCAE) of the National Cancer Institute, version 4.0.

The following safety assessments will be performed at the time points summarized for the study as a whole in Section 6.

The minimum tests required for toxicity evaluation are as follows:

#### Physical examination

- The physical examination is to include a review of all organ systems, an examination of pertinent organ systems, measurement of vital signs (heart rate, BP, and temperature), and measurement of weight and height (height is to be measured at screening only).
- All study BP measurements should be performed in a consistent manner using the same arm for all evaluations and a manual BP cuff. The subject should sit comfortably for 5 minutes with feet on the floor and the arm supported at heart level prior to assessing BP. Two additional BP measurements, taken 5 minutes apart, should be conducted if the first SBP/DBP reading is > 140/90 mm Hg.

#### Blood pressure monitoring and Laboratory evaluations

BP values and clinical laboratory evaluations will be performed by a local laboratory at specified time points during the study as described in Table 5.

**Table 7: Clinical laboratory evaluations**

| Laboratory evaluation                                                                                                                                                                                                                                                                                                                                                                                                                                                                                                                                                                                                                                                                         | Parameters assessed                                                                                                                                                                         |
|-----------------------------------------------------------------------------------------------------------------------------------------------------------------------------------------------------------------------------------------------------------------------------------------------------------------------------------------------------------------------------------------------------------------------------------------------------------------------------------------------------------------------------------------------------------------------------------------------------------------------------------------------------------------------------------------------|---------------------------------------------------------------------------------------------------------------------------------------------------------------------------------------------|
| CBC with differential                                                                                                                                                                                                                                                                                                                                                                                                                                                                                                                                                                                                                                                                         | RBC count, hemoglobin, hematocrit, platelet count, WBC count with differential counts of neutrophils, lymphocytes, monocytes, basophils, and eosinophils                                    |
| Electrolytes                                                                                                                                                                                                                                                                                                                                                                                                                                                                                                                                                                                                                                                                                  | sodium, potassium, and chloride                                                                                                                                                             |
| Chemistry                                                                                                                                                                                                                                                                                                                                                                                                                                                                                                                                                                                                                                                                                     | ALT, AST, bilirubin, alkaline phosphatase, triglycerides, uric acid, total protein, albumin, calcium, lipase, phosphate, lactic dehydrogenase, glucose, creatinine, and blood urea nitrogen |
| Urinalysis via dipstickc                                                                                                                                                                                                                                                                                                                                                                                                                                                                                                                                                                                                                                                                      | urine appearance, pH, glucose, ketones, erythrocytes, leukocyte esterase, nitrite, bilirubin, urobilinogen, protein, creatinine, protein/creatinine ratio, GFRd                             |
| Coagulation panel                                                                                                                                                                                                                                                                                                                                                                                                                                                                                                                                                                                                                                                                             | PT-INR and aPTTd                                                                                                                                                                            |
| 
a. Specified platelet count (<math>\geq 100,000</math> cells/mm^3), hemoglobin concentration (<math>\geq 9</math> g/dL), and absolute neutrophil count (<math>\geq 1500</math> cells/mm^3) without transfusion, or G-CSF and other hematopoietic growth factors must be met at study entry.
 
b. ALT, AST, and bilirubin must be obtained at baseline and monitored weekly for the first 2 cycles (ie, on Days 1, 8, 15, and 22 of Cycles 1 and 2 [<math>\pm 3</math> days]), even if values are normal. The investigators may use investigational site or local laboratory AST, ALT, and bilirubin values for subject treatment decisions; these values must
 |                                                                                                                                                                                             |

- be entered in the eCRF.
- c. Microscopic analysis and proteinuria quantification may be done if the urine dipstick test shows a change from normal.
  - d. Will be measured according to the MDRD-abbreviated formula. GFR calculations must be done within 7 days of study start, then on Day 1 of the first 6 cycles, and at End-of-treatment.
  - e. If a subject is taking warfarin or heparin with stable PT-INR at baseline, close monitoring of PT-INR and aPTT should be performed  $\geq 1$  times/week until PT-INR and aPTT are stable as compared with a pre-dose measurement (defined by the local standard of care).

### 8.3. Intensity of adverse events

The severity (or intensity) of AEs should be documented using CTCAE v 4.0. If no exact matching code is available in CTCAE v 4.0, the following guide should be used:

- CTC 1 = Mild AE: Transient in nature and generally not interfering with normal activities
- CTC 2 = Moderate AE: Sufficiently discomforting to interfere with normal activities
- CTC 3 = Severe AE: Prevents normal activities
- CTC 4 = Life-threatening and/or disabling AE
- CTC 5 = Results in death (fatal)

### 8.4. Collection and reporting of serious adverse events (SAE)

All serious adverse events occurring during treatment or until 60 days after surgery must be recorded and reported using the **serious adverse event report form** (SAE form - see enclosures).

The Investigator must immediately report to the sponsor all serious adverse events. The report should be made using the SAE form online or by sending the paper copy by fax ([name]) to the coordinating office immediately and not exceeding 24 hours following knowledge of the SAE.

All SAE must be also reported in the toxicity case report form within the corresponding CTCAE term.

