## 5. TREATMENT PLAN

### 5.1. Regorafenib treatment

Patients will receive regorafenib orally 160 mg once daily for the first 3 weeks of each 4-week cycle.

Treatment will be definitively stopped in case of disease progression, unacceptable toxic effects, motivated decision to stop the treatment by the treating physician, or refusal or withdrawal of consent by the patient.

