### 5.3. Definitive interruption of study treatment

A subject can definitively interrupt study treatment for the following reasons:

- Unequivocal progression of disease as demonstrated on a CT/MRI scan. In the case of equivocal lesions, subjects should continue to receive study drug until progression is confirmed (CT/MRI scan, follow-up).
- If, in the investigator's opinion, continuation in the study would be harmful to the subject's well-being
- At his/her own request or at the request of his/her legally acceptable representative. At any time during study treatment and without giving a reason, a subject or his/her legally acceptable representative may decline further study treatment. The subject will not suffer any disadvantage as a result. The subject will continue to be followed up for safety and survival unless he/she withdraws consent.
- Study drug dose reduction by more than two dose levels
- Study drug dose interruption for more than one cycle (4 consecutive weeks; maximum of 5 weeks between doses of regorafenib)
- Severe allergic reactions, such as exfoliate erythroderma, anaphylaxis, or vascular collapse
- Any other adverse reaction deemed sufficiently serious to warrant discontinuation of treatment by the investigator
- If female, a pregnancy test result consistent with pregnancy
- Use of illicit drugs or other substances that may, in the opinion of the investigator, have a reasonable chance of contributing to toxicity or otherwise confounding the results of the study
- Development of any intercurrent illness or situation that may, in the judgment of the investigator affect assessments of clinical status and study endpoints to a relevant degree
- Development of a second malignancy except for cervical cancer in situ, nonmelanoma skin cancer, or superficial bladder tumors classified as noninvasive tumor (Ta), carcinoma in situ (Tis), or tumor invades lamina propria (T1).
- Any subject who definitively interrupt study treatment will be evaluated at the End-of-treatment Visit conducted 30 days ( $\pm 7$  days) after permanently stopping study treatment.
- In all cases, the reason for definitive interruption of study treatment must be entered in the electronic Case Report Form (eCRF) and in the subject's medical records.

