### 6.3 End-of-treatment visit

The End-of-Treatment assessments should be performed no later than 14 days after study treatment has stopped.

- Determination of disease status: see paragraph 7 (*Response Evaluation*)
- 12-lead ECG
- Documentation of AEs (CTCAE v 4.0 grading)
- Concomitant medications
- ECOG performance status
- Physical examination, including BP measurement
- The following laboratory evaluations will be performed
  - CBC with differential
  - Chemistry and electrolyte panels

- A coagulation panel, including PT-INR and aPTT
- GFR calculation
- AST, ALT, and bilirubin
- Perform drug accountability

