#### 8.5. Assessments and documentation of adverse events

All AEs occurring from the time the subject has signed the ICF until 30 ( $\pm 7$ ) days after the last dose of study drug (Safety Follow-up) must be entered in the subject's eCRF and coded according to CTCAE v 4.0.

Documentation of an AE must be supported by an entry in the subject's medical file.

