### 9.2. Secondary endpoints

- Toxicity: for each patient and for each type of toxicity, the worst degree suffered during treatment will be described.
- Objective response rate: defined as the number of complete plus partial responses divided by the number of patients enrolled.
- Progression free-survival: defined as the time from registration to progression or death without progression, whichever occurred first. Patients without progression at the end of the study will be censored at the date of the last visit when eventual progression was verified.
- Overall survival: defined as the time from registration to the date of death due to any cause. Patients still alive at the end of the study will be censored on the date of the last information on vital status.
- Metabolic response: defined as a reduction  $\geq 50\%$  of SUVmax after 2 weeks of treatment.

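### The SAE-form window in Section 8.4 is anchored on surgery that is not part of this trial and conflicts with Section 8.5 and Table 6 note h; the Section 9.2 toxicity summary is worded more narrowly than the data collected

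*Protocol*

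**What the plan says.** **SAE form.** Protocol Section 8.4 opens with the only sentence in that section that gives a time window: "All serious adverse events occurring during treatment or until 60 days after surgery must be recorded and reported". The next sentence gives a duty without a window, to be met within 24 hours of learning of the event: "The Investigator must immediately report to the sponsor all serious adverse events". The section closes with "All SAE must be also reported in the toxicity case report form within the corresponding CTCAE term".

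**Adverse events in general.** Section 8.5 begins "All AEs occurring from the time the subject has signed the ICF until 30" and continues to (±7) days past the final dose; these events go into the eCRF. Table 6 note h gives the same start and a 30-day end, and leaves SAEs during later follow-up to the investigator's discretion. Table 6 marks adverse events at the Safety Follow-up visit, and note r applies that visit to everyone who discontinues, for whatever reason.

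**Toxicity endpoint.** Section 9.2: "for each patient and for each type of toxicity, the worst degree suffered during treatment will be described".

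**End-of-treatment visit.** Section 6.3 (End-of-treatment visit): "The End-of-Treatment assessments should be performed no later than 14 days after study treatment has stopped". Section 5.3 says that a patient who stops for good "will be evaluated at the End-of-treatment Visit conducted 30 days" (±7) after stopping.

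**The concern.** A reporting window needs an anchor that occurs in the trial. Here the treatment is described as "Patients will receive regorafenib orally 160 mg once daily for the first 3 weeks of each 4-week cycle", and Section 5.5.1 bars disease-specific surgery during study treatment. Surgery appears elsewhere only as prior history in the exclusion criteria and as pre-planned procedures in the adverse-event definitions. The surgical clause in 8.4 therefore has nothing to attach to, and only *during treatment* is left.

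The 24-hour duty for SAEs sits in 8.4; an eCRF entry under 8.5 carries no such clock. The coordinating centre's SUSAR assessment in Section 8.7 depends on these reports. If one site reads 8.4 as limited by its first sentence and another by its second, an SAE before the first dose or after the last dose may be expedited at one and only entered in the eCRF at the other.

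Toxicity is also a declared secondary aim (Section 2.2). If its summary stops earlier than collection, a toxicity that ends treatment and peaks after the last tablet is recorded but not described at its worst grade.

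**Working it through.** The plan gives no figure to reproduce. The check sets the windows side by side.

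| Rule | Start | End |
|---|---|---|
| SAE form, 8.4, first sentence | during treatment | end of treatment, or 60 days after surgery (no surgery planned) |
| SAE report, 8.4, second sentence | not stated | not stated |
| AE entry in eCRF, 8.5 | consent | 30 (±7) days after last dose |
| AE assessment, Table 6 note h | consent | 30 days after last dose; SAEs later at discretion |
| Toxicity summary, 9.2 | during treatment | during treatment |

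**Step 1: the end of the SAE-form window.** With no surgery, the first row ends when treatment ends, and the Protocol does not define that moment. Cycles contain an off-drug week, and up to 5 weeks may pass between doses.

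**Step 2: conflict with 8.5 and note h.** In 8.5 the end falls between 30 − 7 = 23 and 30 + 7 = 37 days after the last dose. The first sentence of 8.4 ends earlier and starts later (treatment rather than consent). The rules differ at both ends.

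**Step 3: are late SAEs lost?** No. Every SAE is an adverse event, so 8.5, note h, the Table 6 visit grid and note r require it to be recorded through the safety follow-up. What is unclear is whether the 24-hour route applies, because the first sentence of 8.4 limits the time and the second does not.

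**Step 4: the gap in the toxicity summary.** The size depends on where *during treatment* ends, which is an assumption:

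- At the last dose: the 30-day follow-up is omitted, range 23 to 37 days.
- At the end of the off-week, after a full 3 weeks of dosing: 30 − 7 = 23 days omitted, range 23 − 7 = 16 to 37 − 7 = 30.
- At an end-of-treatment visit on day 14, the latest that Section 6.3 allows, counting from the last dose: 30 − 14 = 16 days omitted, range 23 − 14 = 9 to 37 − 14 = 23.
- At the end-of-treatment visit as timed in Section 5.3: essentially nothing omitted.

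**Step 5: the visit timing.** Section 5.3 allows day 23 at the earliest; Section 6.3 allows day 14 at the latest. As 23 − 14 = 9, the windows are 9 days apart and no date meets both. Table 6 has two separate visits, end of treatment and a safety follow-up at 30 (±7) days, which Section 5.3 appears to merge.

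**The case against.** The strongest case on the other side is that the surgical clause is stray text with little practical effect. Section 8.5, note h and note r already secure recording through the safety follow-up. The second sentence of 8.4 covers all SAEs with no time limit, and the SUSAR duties in Section 8.7 have none either. Section 6.3 (Follow-up) follows every patient until death, and Section 7.6 has a response category for early toxic death. How post-dose events enter the tables may be settled in a statistical analysis plan that is not shown. The visit mismatch may be a mislabelled visit.

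Much of this stands, and it limits the point. A reader might infer that serious events after the last dose fall outside the safety rules altogether, or that a late toxic death need not be reported within 24 hours. The Protocol does not support either inference: recording is required, and one sentence of 8.4 demands immediate reporting of every SAE. Nor does it show that post-dose data are discarded, since *during treatment* is undefined.

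What the objection does not remove is the contradiction. The one sentence that sets a window for the SAE form refers to an event that is not part of this trial and disagrees with two other rules. Section 9.2 is a definition stated in the Protocol, not a detail left for later, and its wording is narrower than collection.

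**Conclusion.** The point holds as an internal contradiction in the expedited-reporting window. The first sentence of Section 8.4 has no workable end after the last dose and conflicts at both ends with Section 8.5 and Table 6 note h. The ambiguity applies to every treated patient (up to 46 evaluable patients planned) and to consented patients before their first dose.

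The toxicity summary in Section 9.2, read literally, omits post-dose toxicity that the Protocol collects: 23 to 37 days per patient if treatment ends at the last dose, less under the wider readings above. The number of events involved cannot be derived from the Protocol.

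The end-of-treatment visit has two timings that cannot both be met. This is a supporting correction, relevant because it blurs the end of treatment further.

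None of this touches the primary endpoint or the two-stage decision rules. The conclusion assumes only that no surgery belongs to the trial, which Sections 5.1, 5.5.1 and 6 bear out.

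**What to change.** 1. **Section 8.4:** replace the surgical anchor with the window already used in Section 8.5 and Table 6 note h, from consent to 30 days after the last dose, with the ±7 stated the same way in all three places. Make clear that the 24-hour duty covers that window. Any duty beyond it is for the sponsor to decide; note h at present leaves later SAEs to discretion.
2. **Section 9.2:** let the worst-grade summary run through the 30-day safety follow-up, so that collected post-dose events are described.
3. **Sections 5.3 and 6.3 and Table 6:** reconcile them so that the end-of-treatment visit and the safety follow-up visit each have one timing. Which timing applies is for the sponsor.

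The cost is a wording amendment. The adverse-event data are already collected and no new visit is needed. Reported toxicity may be slightly higher, because events after the last dose would now count.

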#### 8.4.1. Causality assessment between treatment and event

The following criteria will be used for causality assessment:

| Term    | Description                                                                                                                                                                                                                                                                                                                                                                                                                      |
|---------|----------------------------------------------------------------------------------------------------------------------------------------------------------------------------------------------------------------------------------------------------------------------------------------------------------------------------------------------------------------------------------------------------------------------------------|
| CERTAIN | A clinical event, including laboratory test abnormality, occurring in a plausible time relationship to drug administration, and which cannot be explained by concurrent disease or other drugs or chemicals. The response to withdrawal of the drug (dechallenge) should be clinically plausible. The event must be definitive pharmacologically or phenomenologically, using a satisfactory rechallenge procedure if necessary. |

|                                 |                                                                                                                                                                                                                                                                                                                                                         |
|---------------------------------|---------------------------------------------------------------------------------------------------------------------------------------------------------------------------------------------------------------------------------------------------------------------------------------------------------------------------------------------------------|
| PROBABLE/
LIKELY             | A clinical event, including laboratory test abnormality, with a reasonable time sequence to administration of the drug, unlikely to be attributed to concurrent disease or other drugs or chemicals, and which follows a clinically reasonable response on withdrawal (dechallenge). Rechallenge information is not required to fulfil this definition. |
| POSSIBLE                        | A clinical event, including laboratory test abnormality, with a reasonable time sequence to administration of the drug, but which could also be explained by concurrent disease or other drugs or chemicals. Information on drug withdrawal may be lacking or unclear.                                                                                  |
| UNLIKELY                        | A clinical event, including laboratory test abnormality, with a temporal relationship to drug administration which makes a causal relationship improbable, and in which other drugs, chemicals or underlying disease provide plausible explanations.                                                                                                    |
| NOT RELATED                     | There is no causal relationship between the treatment and the event                                                                                                                                                                                                                                                                                     |
| CONDITIONAL/
UNCLASSIFIED    | A clinical event, including laboratory test abnormality, reported as an adverse reaction, about which more data is essential for a proper assessment or the additional data are under examination.                                                                                                                                                      |
| UNASSESSIBLE/
UNCLASSIFIABLE | A report suggesting an adverse reaction which cannot be judged because information is insufficient or contradictory, and which cannot be supplemented or verified.                                                                                                                                                                                      |

